### Legal and ethical aspects

All relevant databases are accessible and the collection of data in these registries has been undertaken in accordance with the generally accepted ethical principles for informed consent and according to the Declaration of Helsinki. Furthermore, all data collection has been approved by the relevant ethical committees in accordance with Danish law. The access and linkage permission from the Danish Data Protection Agency to provide access to the Danish Civil Registration System, where individual civil registration numbers are stored, has already been granted (J. no.: 2010-41-4485). This permission includes merging civil registration numbers with different nationwide disease registers. Statistics Denmark will create the relevant sub-datasets, but before access is allowed the civil registration numbers are hidden. Permission to access and analyze the DBS samples from the Biological Specimen Bank for Neonatal Screening has also been granted by the Ethical Committee D of the Capital Region of Denmark (J. no.: H-3-2011-126).

## Discussion

### Strengths and limitations

The study takes advantage of a vitamin D fortification policy implemented in Denmark almost fifty years ago, and nests this “societal experiment” in a setting where the effect of conditions from conception (and before) for development of certain diseases can be followed among individuals from birth through adulthood. The study is also possible due to complete registration of every citizen in Denmark via a civil registration number. This number can be linked, on an individual level, to the Danish birth, patient and medical registries; social and ethnic registries; and clinical and other large databases. The comprehensive linkage of different datasets makes it possible to study the mediation, confounding or modification of effects of vitamin D for selected conditions through the development of sophisticated models in which individuals can be followed for periods of up to 50 years. Moreover, the large number of subjects that will be followed ensures that the effects of vitamin D exposure in relation to the timing of the seasons and gestational development can also be examined. Nevertheless, the proposed study design implies several uncertainties, including so-called ecological fallacies, addressed below.

Fortification supplied 15% of vitamin D intake on average, which may be considered low, particularly when the sun exposure is not ample. However, vitamin D fortification is especially beneficial when vitamin D status is low [9], e.g. when the previous 6 months of UVB radiation from sun exposure in Denmark was too weak to induce vitamin D conversion in the skin [30]. The use of 50,000-100,000 individuals from adjacent birth years in the general population studies of events like fractures and diagnosis of T1D, a pivotal strength of this study, makes it possible to detect even minor effects of vitamin D.

Food disappearance statistics show that margarine intake decreased and low fat milk slightly increased during the period covered. Nevertheless, changes of this nature are not expected to influence results, because the intervention group and the control group will have been born in adjacent years. Moreover, any societal changes succeeding the initiation of mandatory fortification in 1961 or its termination in 1985 may influence the intervention and control groups similarly. Thus, we find it unlikely that changes in occurrence in the outcomes associated with the introduction and cessation of fortification will lead to spurious conclusions.

We do not collect any individual data on vitamin D intake. In contrary, the individuals in the database are unselected in relation to vitamin D exposure as well as to later disease occurrence. While assuming no ecological fallacies, this in fact may be considered a very strong feature of the present study. Neither confounding from external or internal factors, nor the lack of individual data on vitamin D intake, is a prerequisite for the study, as the influences of lifestyle differences (e.g. use of infant formula, individual diet intake, use of supplements) or societal changes (e.g. in breast feeding, fortified infant formulas, sun exposure) are independent of the vitamin D intervention.

We acknowledge, however, that the differences in prenatal exposure by any subsequent age imply a more simple difference in duration of exposure. Therefore, we will conduct robustness analyses where the age scale is adjusted so that the duration of exposure becomes the same and the difference then only whether the exposure was commenced/ended prenatal or postnatal.

Moreover, there might be regional and urban/rural differences in vitamin D intake. As information on individual’s place of residence is available from Statistics Denmark, it will be included into analyses.

As diet is usually different between families with higher socioeconomic status and those with lower status [31], maternal socioeconomic status may have affected margarine/milk intake and thus exposure to vitamin D. Information on socioeconomic position, education and ethnicity is available from Statistics Denmark and can be controlled for. Adjustments will also be made for maternal age, parity, gestational age and birth weight, which is information available from the birth and patient registries and Statistics Denmark (since 1973, 1977 & 1980, respectively).

Finally, the uncertainties related to lack of knowledge about real vitamin D status in mother and offspring may be eliminated by assessing the measurement of infant blood vitamin D levels in those developing the three disease entities and comparing to time and gender-matched controls to examine actual exposure differences at birth.

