### Vitamin D

Vitamin D is a fat-soluble vitamin that is necessary for the human body. It plays an important role in a wide variety of chronic health conditions. The discovery of high-affinity vitamin D receptors (VDR) in many organs and cell types has led to an increasing focus on the role of vitamin D as a steroid hormone with significant influences on cell metabolism and proliferation. Widely distributed in body tissues, a VDR, once bound to a vitamin D ligand, travels to the nucleus where it binds to sites within the human genome and consequently influences the activity, or expression, of individual genes. A recent study reported identification of as many as 2,776 sites of vitamin D receptor binding and 229 genes whose expression was directly linked to changes in vitamin D levels [2]. Many of these genes are involved in bone and muscle development, metabolism and immune function. Consequently, low vitamin D influences bone health, body growth and composition, and also impacts on immunity [3,4]. Furthermore, as proposed in 2001, a critical window may exist during which vitamin D levels have a persisting impact on health outcomes [5]. Low vitamin D during gestation and in early life may therefore play an important role for susceptibility to bone fragility, obesity and autoimmune diseases later in life [6].

Vitamin D is synthesized in the skin when exposed to ultraviolet-B radiation from the sun. 7-dehydro-cholesterol is converted to cholecalciferol (vitamin D3) which is then, in kidneys, modified further to form the active vitamin binding to VDR. Animal tissues consumed as food provide additional sources of this hormone-like vitamin, while plant foods may provide the less potent form of vitamin D: ergocalciferol (vitamin D2) [7]. Although adequate exposure to UVB sunlight is paramount to an ample supply of vitamin D, oral intake, augmented by both fortification and supplementation, is necessary to maintain baseline stores in populations at high latitudes were the sun can only drive dermal synthesis of vitamin D from April to October [8]. It has been shown that fortification is particularly relevant for those with low stores, e.g. pregnant women [9].

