#### Perinatal exposure

Development of the disease outcomes will be compared for children born around the time when mandatory vitamin D fortification was initiated and terminated. The hypothesis is that individuals born 1–2 years after commencement of mandatory fortification (1961) and thus exposed to extra vitamin D during fetal development and for the next 24–25 years until 1985 (where fortification was ended), although unexposed thereafter, will have a lower lifetime risk of developing the aforementioned disease entities compared to individuals born 1 –2 years before fortification. Although also exposed to fortification for 24 – 25 years and unexposed thereafter, the latter group was unexposed during fetal life. Likewise, individuals born 1–2 years after mandatory fortification terminated in 1985, and who were unexposed to vitamin D both during fetal development and subsequently, will have a higher risk of later developing the diseases compared to those exposed during fetal life. Similar comparisons of disease development can be made in relation to higher exposure to vitamin D from 1972–1976, when fortified low fat milk was permitted.

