#### Seasonal variation in vitamin D exposure

The extra vitamin D from fortification is expected to be of particular relevance when stores are low [9]. To study seasonal variations, large datasets are needed and will be created by including individuals from 2–4 birth cohorts born before and after fortification. Whether or not exposure to vitamin D fortification in different gestational trimesters is important will be examined. For instance, influence of low vitamin D on obesity and adipose tissues may be particularly important for children whose third gestation periods occur during winter, while influence of low vitamin D on autoimmune diseases may be particularly important for children whose first gestational trimester occurs during winter.

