### Power calculation

In relation to long-term health effects of initiation (or termination) of the fortification, analyses including continuous outcomes, such as BMI, will not present power problems. For incidence of obesity, fractures and T1D, calculating the least detectable excess risk is relevant. The power calculation is done generically in a worst-case scenario using a dichotomous outcome with a low prevalence. The least detectable excess risk is calculated assuming that either one (at least 50,000 individuals) or two birth cohorts are included. As the follow-up period varies, the final prevalence (= incidence × duration) will be used and varied from 1-8%. The significance level is α = 0.05 and power β = 0.80. Table 1 shows the least detectable relative risk of outcome after change in fortification.

**Table 1 T1:** Least detectable relative risk of outcomes in relation to exposure to foods fortified with vitamin D

**N (exposed/non-exposed)**	**Prevalence of outcome (fractures, T1D, obesity)**				
	**0.5%**	**1%**	**2%**	**4%**	**8%**
50,000/50,000	1.27	1.19	1.13	1.09	1.07
100,000/100,000	1.19	1.13	1.09	1.07	1.05

For analyses using DBSs, power calculations were performed under 3 scenarios related to the fraction of the exposure variance explained including covariates: no adjustment, 30% explained or 60% explained. Table 2 gives the least detectable hazard ratios (for fractures and diabetes) or odds ratios (for BMI) of outcome related to 1 SD difference in 25(OH)D3 for a sample size of 1000 cases and 1000 controls using α?=?0.05 and β?=?0.80.

**Table 2 T2:** Least detectable hazard ratios (for fractures and diabetes) or odds ratios (for BMI) of outcome related to 1 SD difference in 25(OH)D3 for a sample size of 1000 cases and 1000 controls

**Least detectable Hazard (HR) or Odds rate (OR) ratios related to 1 SD difference in 25(OH)D3**	**1000 cases (obesity, diabetes or fractures) and 1000 time- and gender-matched controls**		
	**No covariates**	**30% variance explained**	**60% variance explained**
OR ratio	1.13	1.16	1.22
HR ratio	1.09	1.11	1.15

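### Independence of sun exposure from the policy does not protect a contrast of one or two birth years per arm from chance year-level imbalance

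*Protocol article*

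**What the plan says.** The Strengths and limitations section argues that confounding does not threaten the study, on the ground that "societal changes (e.g. in breast feeding, fortified infant formulas, sun exposure) are independent of the vitamin D intervention". It also expects societal changes to affect both groups alike, and counts the 50,000–100,000 individuals from neighbouring birth years as a main strength that allows small effects to be seen.

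The Perinatal exposure section defines the main contrast. People born one to two years after mandatory fortification began are "compared to individuals born 1 –2 years before fortification". The mirror contrast is made at termination in 1985, and similar ones around the 1972–1976 milk period. The seasonal analysis is wider, "including individuals from 2–4 birth cohorts born before and after fortification".

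The Power calculation section works "assuming that either one (at least 50,000 individuals) or two birth cohorts are included", and Table 1 follows from that. Statistical analyses names Cox, linear and logistic models with year/month of birth as key covariate, and an unspecified adjustment for secular trends.

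On the importance of sun, the Vitamin D section says "adequate exposure to UVB sunlight is paramount to an ample supply of vitamin D". On the size of the intervention, Strengths and limitations says "Fortification supplied 15% of vitamin D intake on average, which may be considered low".

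**The concern.** Arm is determined by date of birth. Everyone in an arm was carried through the same few summers, and everyone in the comparator through different ones. That the policy was not timed by the weather rules out systematic confounding by sunshine. It does not balance sunshine between one or two particular years before a switch and one or two after it. The unit that varies is the year, so 50,000 births in a year still give one draw of that year's sunshine. The same holds for any other shock specific to a birth year.

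By the article's own account sunlight matters greatly to vitamin D supply and the fortification increment is modest, so the imbalance may be of the same order as the contrast under study. If so, the estimate could be too large, hidden or of the wrong sign, with an interval that reflects only the number of individuals. The results are meant to inform whether fortification should resume, so the reader needs to know how much of an estimate could be year-to-year variation.

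**Working it through.** **1. The plan's own figure.** Inputs from Power calculation: 50,000 or 100,000 per arm, and "The significance level is α = 0.05 and power β = 0.80". Solving the usual two-proportion formula (pooled variance, two-sided 0.05, 80% power) for the relative risk gives:

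| Prevalence | 0.5% | 1% | 2% | 4% | 8% |
|---|---|---|---|---|---|
| 50,000, computed | 1.266 | 1.184 | 1.128 | 1.089 | 1.061 |
| 50,000, Table 1 | 1.27 | 1.19 | 1.13 | 1.09 | 1.07 |
| 100,000, computed | 1.185 | 1.129 | 1.090 | 1.062 | 1.043 |
| 100,000, Table 1 | 1.19 | 1.13 | 1.09 | 1.07 | 1.05 |

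All ten cells agree once rounded up. The formula treats individuals as independent, so the between-year variance in Table 1 is zero.

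**2. Adding a birth-year variance.** Let τ be the SD of log risk between birth years and k the years per arm. Then var(log RR) = SE² + 2τ²/k. The documents give no τ; 0.01–0.05 is assumed. It stands for any year-specific shock to risk and is not derived from sunshine.

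Example at 8% prevalence, 50,000 per arm, k = 1: SE = ln(1.061)/2.80 = 0.0211. With τ = 0.02 the total is √(0.0211² + 2×0.02²) = 0.0353. The true type I error is 2[1 − Φ(1.96×0.0211/0.0353)] = 24%, and the detectable relative risk is exp(2.80×0.0353) = 1.10.

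| Case | τ = 0.01 | τ = 0.02 | τ = 0.05 |
|---|---|---|---|
| 8%, one year per arm: type I error; detectable RR | 10%; 1.07 | 24%; 1.10 | 57%; 1.23 |
| 8%, two years per arm | 10%; 1.05 | 24%; 1.07 | 57%; 1.16 |
| 0.5%, one year per arm | 5.3%; 1.27 | 6.3%; 1.28 | 13%; 1.36 |

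Doubling the births by adding a second year leaves the type I error where it was, because sampling variance and year variance shrink together. For rare outcomes and small τ the effect is slight.

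**3. Sunshine against the fortification contrast.** Let f be the share of total vitamin D supply that comes from intake, and c the yearly SD of sun-derived supply. Both are assumed. Supply is taken as additive and years as independent.

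- Fortification contrast: 0.15f.
- Sunshine difference of equal size: 0.15f/(1 − f), which is 1.7% at f = 10%, 3.75% at 20%, 6.4% at 30%, 15% at 50% and 60% at 80%.
- SD of the chance sunshine difference relative to the contrast: (1 − f)·c·√(2/k)/(0.15f).

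| f | k | c = 5% | c = 10% | c = 15% |
|---|---|---|---|---|
| 10% | 1 | 4.2 | 8.5 | 12.7 |
| 10% | 2 | 3.0 | 6.0 | 9.0 |
| 20% | 1 | 1.9 | 3.8 | 5.7 |
| 20% | 2 | 1.3 | 2.7 | 4.0 |
| 50% | 1 | 0.47 | 0.94 | 1.41 |
| 50% | 2 | 0.33 | 0.67 | 1.0 |
| 80% | 1 | 0.12 | 0.24 | 0.35 |
| 80% | 2 | 0.08 | 0.17 | 0.25 |

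At f = 50% and c = 10%, the chance that the sunshine difference is at least as large as the fortification contrast, in either direction, is 29% with one year per arm and 13% with two. Half of that cancels or reverses the contrast; the other half at least doubles it. At f = 20% and c = 10% the chances are 79% and 71%. At f = 80% the chance is at most 0.5%.

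**4. What the contrast can reveal about its own error.** One year per arm leaves 0 degrees of freedom for between-year variation. Two years per arm leave 2, for which the critical value is 4.30 rather than 1.96.

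**The case against.** - **The size rests on assumption.** The article gives neither the sun share of supply nor yearly sunshine variation. It calls UVB paramount, but the same sentence says that oral intake is needed to maintain stores at high latitude. A reader might infer that sunshine is the main source; no share is stated. This objection stands, and it is why the table runs to f = 80%, where the problem is negligible.
- **A false positive does not follow from sunshine alone.** A reader might infer that a sunny or dull year could create a fortification effect where none exists. On the path from sunshine through vitamin D to outcome it cannot: if vitamin D does not matter, sunshine produces no outcome difference by that path. What follows is a masked, inflated or reversed effect. The type I error figures concern year shocks in general, for an assumed τ.
- **The seasonal analysis.** A reader might infer that it suffers most. It uses 2–4 birth cohorts rather than 1–2, and it looks for the effect when status is low after months of weak UVB. Carry-over from the previous summer is possible, but nothing computed here shows that this analysis is worse affected.
- **The sentence may mean behaviour, not weather.** Sun exposure stands there beside breast feeding and infant formula. That is a fair reading, but the sentence is still used to dismiss confounding in general, and chance imbalance between years is not mentioned.
- **Safeguards exist.** The 1961 and 1985 contrasts predict opposite directions, so unrelated shocks would have to line up by luck to imitate a consistent effect. This is a real but partial protection. It is not made a condition for any conclusion, and it is unavailable for type 1 diabetes, whose registry starts with 1981 births. Other features do not help here. A smooth trend term does not remove irregular yearly shocks. Sibling pairs straddle the switch by design. Blood-spot controls are matched on exact date of birth, which takes out between-year differences; that helps the test of the vitamin D hypothesis but does not validate the before–after contrast.

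**Conclusion.** The concern holds in a limited form. Independence from the policy is a statement about expectation, and arms of one or two birth years do not average out year-specific shocks. Table 1, and intervals from the models as described, carry no allowance for them, so the stated precision may be too optimistic.

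How much too optimistic cannot be settled from the documents. For an assumed 5–15% yearly sunshine SD, the chance sunshine difference ranges from 0.08 times the fortification contrast (intake 80% of supply) to several times it (intake 10–20%). The calculation assumes additive supply, independent years and the stated 15% of intake. It shows that the imbalance can matter, not that it did. The point is worth correcting because the linked cohorts can measure the year-to-year variation directly.

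**What to change.** 1. In Strengths and limitations, limit the statement to independence in expectation, and acknowledge that one or two birth years per arm can differ by chance in sunshine and other year-specific factors.
2. Repeat the identical adjacent-year contrast at dates with no switch, within the linked birth cohorts wherever the outcome registry covers them. Judge the switch estimates against that placebo distribution, or include a birth-year variance component estimated from those years. Neighbouring placebo contrasts share birth years, so their number overstates the information.
3. Report whether the 1961 and 1985 contrasts agree in the predicted opposite directions, where both are available.
4. Optionally, add gestational sunshine hours as a sensitivity analysis, estimated across many non-switch years. It should not be a required covariate in every model: within one or two years per arm it is close to collinear with arm. Whether a suitable national series exists for these years is not stated in the documents.

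The cost is more birth years to analyse, some exposure to longer secular trends in the placebo years, and wider intervals that show the real uncertainty. No new participants or measurements are needed.

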### Implications

Unlike many other nutritional deficiencies, low vitamin D status is prevalent among industrialized populations, and, according to Danish health authorities, about half of all adults have vitamin D insufficiency (below 50 nmol/l) [32]. Adequate exposure to UVB sunlight is paramount importance for supply of vitamin D, but oral intake, augmented by fortification and supplementation, is necessary to maintain baseline stores, particularly in winter when sunlight is limited [8,33,34]. Thus, as it is clear that vitamin D status of Danes needs to be improved, the Danish health authorities currently debate, whether to resume vitamin D fortification of food [35]. The complete lack of knowledge on the general health effects of fortified foods is an important issue in this regard. Our results will significantly increase current understanding of the importance of early vitamin D intake for long-term health and the occurrence of diseases. The results will also provide solid quantitative justification whether to resume vitamin D fortification. From a public health perspective, the potential to prevent common chronic diseases via low-cost, simple and safe food fortification is an attractive option.

Additionally, we expect that the results of the study will open new research opportunities for other scientists and fields, e.g. human intervention studies to determine the level of vitamin D supplementation necessary to reduce susceptibility to diseases later in life and concomitant basic research exploring the biological mechanisms that may be involved. Because it is possible to obtain information in Denmark on individual health and social parameters via linkage to health registries using a unique personal identification number, many opportunities for collaboration will arise in relation to health aspects, e.g. growth and pubertal development, possibility related to vitamin D exposures in early life, perhaps even before conception, in addition to the outcomes studied. If and when our nationwide model is in operation for the three diseases studied, the approach used and the inherent methodologies applied can easily be adapted to study other health outcomes.

